### Inclusion and Exclusion Criteria

To be eligible for participation in this clinical trial, patients must meet specific inclusion criteria, which are as follows: being a healthy male or female; aged 18-35 years old; providing written informed consent to participate in the trial; having an average blood count within normal range; presenting with impacted mandibular third molars that require extraction. The diagnostic indications for tooth extractions include caries, orthodontic, and preventive measures. In particular, based on the relation of the impacted mandibular third molar to the ramus, the impacted teeth will be restricted to Class I and Class II as per the Pell and Gregory classification [20,21]. Patients had to demonstrate good oral hygiene, maintain healthy periodontium, and have a clinical attachment loss score of ≤2 mm and a probing pocket depth (PPD) of <4 mm. Clinical and radiographic images taken before the operation are depicted in Figure 2.

**Figure 2 figure2:**
[figure not shown]
Preoperative image of the clinical and radiographic condition of the patients.

Patients will be disqualified from participating in the study if they meet any of the following exclusion criteria: impacted teeth concerning their position relative to the occlusal plane fall within the Pell and Gregory classification's level C category [20,21]; presence of uncontrolled or untreated periodontal disease; existence of acute abscesses or active infections that occur close to the targeted surgical site; presence of systemic diseases or systemic/local infections; recent receipt of chemotherapy, radiotherapy, immunosuppressant medications, or anticoagulants that could potentially interfere with the healing process; previous administration of bone growth–inducing substances, malnutrition, or current active influenza; regular smoking habit of more than 10 cigarettes per day; being pregnant, breastfeeding, or participating in a fertilization program.

### Withdrawal of Participants

Participants have the right to withdraw from the study at any time and for any reason without facing any negative consequences. In cases where a participant has urgent medical needs, the researcher may choose to exclude them from further participation in the study. Participants who choose to discontinue the study before completing all surgical procedures and follow-up visits will be considered dropouts.

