### Study Design

This prospective control clinical trial will be conducted at a single center and will involve 30 targeted extraction sockets after the removal of impacted mandibular third molars. This case is chosen as it represents a common scenario requiring extraction and often involving the removal of a significant amount of bone, making it an ideal model for studying human alveolar bone loss for socket preservation. The study aims to evaluate the efficacy of a high-purity α-CSH bioceramic (CaSO_4_·0.5H_2_O), synthesized from calcium sulfate dihydrate (CSD) without the use of chemical reagents, as a bone graft material in the alveolar bone loss case.

The 30 extraction sockets will be randomly assigned into 2 groups: 15 will receive α-CSH as a bone graft, while the other 15 will not receive any graft material. The main end point will be evaluated 6 months into the procedure. During follow-up visits, any adverse events or serious adverse events will be carefully documented, and clinical assessments will be conducted as specified in the “intervention section.” All patients will undergo regular monitoring through clinical examinations, radiographs, lab tests, and any additional necessary procedures. Ultimately, the study will publish a comprehensive report on the feasibility and potential efficacy of the α-CSH approach in promoting bone formation, regardless of the outcome.

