### Sample Size

As this study focuses on feasibility rather than achieving statistical significance, formal power calculations were not conducted prior to its initiation. Instead, the emphasis lies on assessing safety, feasibility, and generating preliminary data.

With no prior data on the use of this bone graft material in humans, the sample size was determined based on practical considerations, including resource availability, feasibility of recruitment within the study timeline, and ethical concerns regarding participant risk exposure. The aim was to enroll a sample size, allowing for meaningful observations and providing valuable preliminary insights into safety and efficacy.

Furthermore, following a common rule of thumb for pilot studies, which typically suggest around 30 participants, we decided on a sample size of 30 extractions, with 15 extraction sockets in each group. The number of sockets per patient varies based on individual clinical circumstances. This sample size was deemed appropriate for assessing safety, feasibility, and generating preliminary efficacy data.

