### Randomization and Blinding

The allocation of participants into the treatment and control groups will be determined through randomization. This process will be conducted using a secure computer system for central randomization. Each patient will be assigned a unique study code, and their data will be provided to the operators and research evaluators in a format that preserves patient confidentiality through coding. When evaluating the data, the radiologist and the statistician will be blinded to the treatment.

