### Statistical Analysis

Statistical analysis will be performed using SPSS 16.0 (IBM Corp). Student *t* test will be used to analyze the difference between groups and different follow-up points. The statistical significance level will be set at a *P* value of .05 or lower.

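### The withdrawal rule lets the researcher end a participant's follow-up, after grafting as well as before, for a reason that may itself be a complication of the procedure

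*Protocol article*

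**What the plan says.** Withdrawal of Participants gives two routes out of the trial besides the general right to withdraw.

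- Exclusion by the researcher: "In cases where a participant has urgent medical needs, the researcher may choose to exclude them from further participation in the study". Urgent need is not defined, no link to the study procedure is required or ruled out, and no time limit is given.
- Voluntary discontinuation: "Participants who choose to discontinue the study before completing all surgical procedures and follow-up visits will be considered dropouts". This covers people who choose to stop. Participants excluded by the researcher are not classified.

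Other sections bear on the rule:

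- Study Design: "The main end point will be evaluated 6 months into the procedure". Adverse events are to be documented at follow-up visits. Of the 30 sockets, "15 will receive α-CSH as a bone graft, while the other 15 will not receive any graft material".
- Interventions and Table 1: the graft is placed at a single operation. Follow-up is at days 7, 14, 90 and 180, with CBCT at days 90 and 180.
- Feasibility Assessment: graft loss is assessed both early and late after surgery, and safety is judged by comparing adverse event frequency with the ungrafted arm.
- Randomization and Blinding: "the radiologist and the statistician will be blinded to the treatment". No other role is named as blinded.
- Adverse Event and Severe Adverse Event Assessment: the principal investigator is told of a severe event within 24 hours.
- Posttrial Care: safety follow-up at 1 and 2 years is promised for everyone in the trial.

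**The concern.** In a trial with continuing treatment, an exclusion clause of this kind can be a way to stop treatment. Here the intervention is finished when the wound is closed. From then on, participation consists mainly of being observed, so exclusion mainly ends data collection.

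The trigger may be linked to the outcome. After surgery, an urgent medical need may be an infection, dehiscence or graft loss, and the protocol lists these as feasibility outcomes. The decision is also discretionary, and nothing in the text prevents the person making it from knowing the allocation. Losses could therefore depend on outcome and differ by arm.

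Two things are at stake: adverse events and graft loss occurring after exclusion, and the 6-month measurement. No analysis plan can recover a visit or scan that the protocol allowed to be cancelled.

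**Working it through.** **Does the rule reach the period after grafting?** The clause gives no timing. The sentence after it refers to surgical procedures and follow-up visits together, so the section covers the whole course of the trial. A reading limited to the time before surgery has no support in the text.

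**What does exclusion end after surgery?** Per Table 1, what remains is the visits at days 7, 14, 90 and 180: photographs and physical examination at each, with panoramic imaging, CBCT and probing at days 90 and 180. Study Design ties adverse event documentation to these visits. Ending them ends the stated route for later events and the source of the 6-month end point.

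**Could the decision depend on allocation?** The operators place or withhold the graft, so they know the arm. Only two roles are named as blinded. That the excluding researcher knows the arm is an inference; that nothing prevents it follows from the text.

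**How large could the effect on the 6-month mean be?** The protocol gives no SD, effect size or power figure ("formal power calculations were not conducted prior to its initiation"), so the only stated figure to reproduce is 15 + 15 = 30, which agrees. The rest is an illustration in SD units.

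Inputs:
- 15 sockets per arm (Study Design).
- k = number of sockets in one arm lost through exclusion (assumed 1 to 3).
- D = gap between the mean of the remaining sockets and the mean of the lost sockets, in SD (assumed 0.5 to 2).

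Full-arm mean = [(15 − k) × remaining mean + k × lost mean] / 15 = remaining mean − (k/15) × D.

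The observed mean therefore differs from the full-arm mean by (k/15) × D:

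| k | D = 0.5 | D = 1 | D = 2 |
|---|---|---|---|
| 1 | 0.03 | 0.07 | 0.13 |
| 2 | 0.07 | 0.13 | 0.27 |
| 3 | 0.10 | 0.20 | 0.40 |

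For k = 2: (2/15) × 0.5 = 0.07 and (2/15) × 2 = 0.27 SD. Each socket is 1/15 = 6.7% of its arm. Sample Size says that sockets per patient vary, so excluding one patient could remove more than one socket.

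**Is lost precision the problem?** No. With two-sided 5% significance, 80% power and the normal approximation, the detectable difference is (1.96 + 0.84) × √(1/n₁ + 1/n₂):
- 15 vs 15: 2.80 × √0.1333 = 1.02 SD
- 15 vs 13: 2.80 × √0.1436 = 1.06 SD

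Precision hardly changes. The issue is selection.

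**The case against.** The strongest reply is that the clause ends further participation and nothing more. It does not delete recorded data or discount the event that led to exclusion. Adverse events are documented, severe ones reach the principal investigator within 24 hours, severe toxicity or infection at the site halts the trial, and Posttrial Care promises long-term safety follow-up for everyone. Urgent needs in healthy people aged 18 to 35 may also have nothing to do with the socket. All of this stands. It limits the point to what happens after exclusion. It does not remove the point, because none of these sections says that an excluded participant keeps the scheduled visits and scans.

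Three stronger readings are tempting and not supported:

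- A reader might infer that complications vanish from the safety comparison. For example, 3/15 vs 2/15 (20.0% vs 13.3%) would become 1/13 vs 2/15 (7.7% vs 13.3%) if two event cases were dropped from the α-CSH arm. That requires both the events and the sockets to be erased, which the protocol does not say. Even then the result depends on the counts chosen: 2/14 vs 2/15 (14.3% vs 13.3%) and 2/13 vs 2/15 (15.4% vs 13.3%) do not reverse.
- A reader might infer that every participant who misses a visit becomes a dropout and leaves the comparison. The dropout sentence covers only those who choose to stop.
- A reader might fault the protocol for not fixing the analysis set or the handling of missing values. These may be in an analysis plan or full protocol that is not shown, so their absence is not held against this document.

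**Conclusion.** The point holds in limited form. As written, the clause permits discretionary exclusion, after grafting as well as before, for a reason that may be a complication of the procedure, and it does not separate ending study procedures from ending data collection. It also sits uneasily with the promise in Posttrial Care to follow everyone.

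Later adverse events, late graft-loss assessment and the 3- and 6-month CBCT are at risk; the triggering event is not, if the reporting sections are followed. On assumed values, two lost sockets in one arm shift its 6-month mean by 0.07 to 0.27 SD. This range rests on the assumed D, on both losses falling in the same arm, and on their being missing at 6 months. Similar losses in the other arm would partly cancel in the difference. How often exclusion will occur cannot be judged from the protocol, and it may be rare. This is a cheap improvement worth making.

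**What to change.** Amend Withdrawal of Participants to state that:

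1. exclusion by the researcher ends only the remaining study procedures, not data collection;
2. the excluded participant stays in the randomised arm, and the event that prompted exclusion is counted there;
3. the reason for each exclusion is recorded and reported by arm;
4. adverse event follow-up continues, as do the day-90 and day-180 assessments where feasible and with consent, unless the participant withdraws consent.

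Reconcile this wording with the 1- and 2-year follow-up in Posttrial Care, so that it is clear whether excluded participants are included there. The amendment takes no view on when exclusion is medically warranted or how the participant is treated.

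The cost is a few sentences and continued contact with the few participants excluded, at visits already scheduled.

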### Material Preparations

The high-purity α-CSH bioceramic was synthesized from calcium sulfate dihydrate (Acros Organics, Morris Plains, NJ) using a microwave irradiation technique, following the methodology outlined in our previous study [14,17]. In brief, 2 g of CSD powder were mixed with 10 mL of deionized water. Following this procedure, the resulting mixture, along with a magnetic stirring bar, was placed in a 55-ml Teflon pressure tube at approximately 350 pounds per square inch (psi). The mixture was then subjected to microwave irradiation at 800 watts and 160 °C for 10 minutes. After synthesis, the sample was filtered, washed with ethanol, then dried in an oven at 60 °C for 8 hours, and finally ground into a powder.

### Interventions

Prior to the surgical procedures, a preoperative panoramic x-ray and cone-beam computed tomography (CBCT) scan will be conducted to evaluate the tooth position and the surrounding bone structure. A complete blood count (CBC) will also be performed to ensure the safety of all patients undergoing surgical procedures and receiving bone grafts. Furthermore, the PPD score will be measured using a periodontal probe (BPWHO: Single, Osung, South Korea) to evaluate the periodontal condition. Patients exhibiting a significant amount of calculus will be referred for scaling and root planning procedures. Skilled oral and maxillofacial surgeons will carry out the interventions following standardized operating procedures. Video demonstrating the clinical and surgical procedures will be presented during the initial calibration meeting to ensure consistency across all operators.

The extraction of mandibular third molars will be carried out in a sterile environment under local anesthesia, minimizing damage to both the soft tissue (gingiva) and the hard tissue up to the crest of the bone. The surgery will adhere to the principle of minimally invasive techniques, using a split technique. To preserve the integrity of the marginal alveolar bone, an elevator will be used carefully to avoid any harm to the bone margins. Initially, a triangular access flap was created, with a releasing incision made on the tuberosity and another distal to the second molar. Then, the third molars will be split, and extraction will be performed using forceps or a dental elevator. After removing the tooth, a thorough sharp curettage will be performed to eliminate any remnants of the periodontal ligament and other soft tissues. Special attention will be given during the procedures to protect the socket walls and interproximal papillae from damage.

The fresh extraction sockets will be treated differently based on the assigned groups. In the experimental group, α-CSH material will be used to fill the socket, while no bone graft material will be applied in the control group. The amount of α-CSH used will depend on the size of the socket. Using a periosteal elevator, the material will be carefully placed and gently packed into the extraction site until it reaches the top of the socket. The graft material will be applied up to 2 mm apical to the soft tissue edge, with a maximum total dose of 3 g per patient. A membrane will be used to cover the upper side of the socket, and primary wound closure will be achieved using absorbable sutures.

Postoperatively, patients will be prescribed appropriate antibiotics and pain relievers for a duration of 7 days. They will be provided with instructions to follow a soft food diet, gargle after meals, and limit physical activities for the first 3 days following surgery. Clinical follow-up examinations will be conducted at 7 days and 14 days after the procedure. Control assessments will include panoramic radiography and CBCT scans within 3 and 6 months after the surgery to monitor the progress of bone formation.

### Adverse Event and Severe Adverse Event Assessment

Adverse events encountered during the study will be classified as serious or nonserious based on severity using the classification system established by the World Health Organization [22]. Participants who experience any adverse events will receive comprehensive medical care to address their needs. Any changes in the participant’s health status that occur between

the screening examination and the initial administration of α-CSH or associated procedures will be documented in their medical records. In the event of a severe adverse event, the principal investigator will be promptly notified within 24 hours of its occurrence. If the severe adverse event is determined to be associated with severe toxicity or infection at the transplant site, the experiment will be immediately halted to ensure participant safety.

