### Data Collection and Access

The study team will receive detailed guidelines and responsibilities. The medical professionals within the research team will collect the required information as outlined in Table 1. Training sessions will be conducted for the entire research team to ensure consistent data collection at each study visit. The clinical assessors and investigators will receive the data in a format that maintains patient confidentiality through coding. The participants will be monitored for a maximum duration of 6 months. The data manager will prioritize the confidentiality and security of the participant's data.

**Table 1 table1:** Assessment of clinical trial.

	Consent form	Clinical photograph	Panoramic	CBCT^a^	Blood test	Probing	Physical examination
Preoperatively	✓	—^b^	✓	✓	✓	✓	✓
Operative day	—	✓	—	—	—	—	✓
Postop day 7	—	✓	—	—	—	—	✓
Postop day 14	—	✓	—	—	—	—	✓
Postop day 90	—	✓	✓	✓	—	✓	✓
Postop day 180	—	✓	✓	✓	—	✓	✓

^a^CBCT: cone-beam computed tomography.

^b^Not applicable.

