### Outcomes

#### Feasibility Assessment

The assessment of α-CSH safety in the present context will focus on the occurrence of serious adverse events. To deem α-CSH as safe, it should not result in a higher frequency of adverse events compared to standard treatment (without socket preservation). Additionally, any adverse events that do arise should be manageable through established noninvasive procedures such as analgesics and antibiotics. The evaluation of safety will play a crucial role in determining the suitability and viability of α-CSH in the study.

Feasibility evaluation was conducted using intraoral clinical examination and photographs to assess potential complications such as inflammation, infection, dehiscence, and graft loss. Graft loss will be evaluated in the early postoperative period, within the first week, and late postoperative period. The progress of wound healing at the surgical sites will be assessed with the Landry wound healing index [23]. This index considers factors such as the color of the soft tissue (pink or red), presence of suppuration, amount of bleeding, presence of granulation tissue, and exposure of connective tissue. Based on these criteria, the healing process was categorized into 5 distinct categories, namely very poor, poor, good, very good, and excellent [23]. Patients were also asked about any pain in the surgical site or adjacent areas during the follow-up period.

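### The adverse-event section defines seriousness by severity and ties the 24-hour notice and the halting rule to a severe, not a serious, adverse event

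*Protocol article*

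**What the plan says.** The Protocol article deals with the grading and handling of adverse events in the section Adverse Event and Severe Adverse Event Assessment. Three statements there matter:

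- Classification: events are "classified as serious or nonserious based on severity using the classification system established by the World Health Organization".
- Notice: "In the event of a severe adverse event, the principal investigator will be promptly notified within 24 hours of its occurrence".
- Halt: "If the severe adverse event is determined to be associated with severe toxicity or infection at the transplant site, the experiment will be immediately halted".

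Two other sections use a different term for the higher class. Study Design says that "any adverse events or serious adverse events will be carefully documented". Feasibility Assessment says that the safety assessment "will focus on the occurrence of serious adverse events". It adds a criterion for calling the material safe, namely that "it should not result in a higher frequency of adverse events compared to standard treatment".

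Sample Size states that there are no earlier data on this graft material in humans. Monitoring states that there will be no separate Data Safety Monitoring Board. It relies on internal monitors for ethical compliance and on an annual safety report.

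**The concern.** Seriousness and severity are separate attributes of an adverse event. An event is serious because of its consequence: death, threat to life, hospital admission or lasting disability. It is severe because of its intensity. Either can occur without the other. A bad headache may be severe and not serious; a short admission for a moderate infection is serious and not severe.

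The classification sentence makes the first attribute depend on the second, and the two action rules then use the intensity word. Taken as written, the rules can pass over an event that is serious by outcome but not intense. The principal investigator need not hear of it within 24 hours, and it need not be weighed against the halting condition.

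This matters more here than in a trial of an established product. The material has no earlier human data, and no separate board reviews safety. The two sentences are the document's only stated rule for telling the principal investigator about an individual event and its only stated stopping rule.

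**Working it through.** No arithmetic applies: the plan gives no event rate, and the point concerns definitions and triggers. The check sets the statements side by side.

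**Terms used for the higher class of event**

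| Place in the Protocol article | Term |
|---|---|
| Adverse Event section, heading | severe |
| Adverse Event section, classification sentence | serious, decided by severity |
| Adverse Event section, 24-hour notice | severe |
| Adverse Event section, halting sentence | severe |
| Study Design, documentation of events | serious |
| Feasibility Assessment, safety focus | serious |

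No section says that the two words mean the same, and none defines seriousness by outcome.

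**Test case.** Take an event that is serious by outcome but mild or moderate in intensity. The Recruitment section lists infection and injury to facial nerve branches among the risks. A short admission for a moderate infection, or a mild but lasting nerve deficit, would fit.

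1. *Classification.* If severity decides, the event is filed as nonserious. If the cited World Health Organization system is outcome-based and overrides the wording, it is filed as serious.
2. *Notice.* If severe means intense, no notice is required, however the event was filed. If severe is a synonym for serious, notice is required only if step 1 filed the event as serious.
3. *Halt.* The halting sentence starts from the same severe adverse event, so an event that fails step 2 is not considered under it.

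The notice therefore reaches such an event only if the words are synonyms **and** the cited system is outcome-based. The text states neither.

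**What else would catch the event.** Interventions says that "Clinical follow-up examinations will be conducted at 7 days and 14 days after the procedure", and the assessment table in Data Collection and Access adds visits at day 90 and at "Postop day 180". After day 14 the scheduled visits are 90 − 14 = 76 days and 180 − 90 = 90 days apart. The event would be documented at a visit, but nothing in the article says that visit records, the ethics monitors or the annual report prompt notice to the principal investigator or consideration of a halt. The gaps show only that scheduled visits do not replace a 24-hour rule. They do not measure a delay.

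**The case against.** The best reply is that the troubling reading is not the natural one. The section sets up two classes, serious and nonserious, and no mild, moderate and severe grades. A severe adverse event distinct from a serious one would be a class that the document never creates. The section heading also parallels the pairing in Study Design. Severe is thus most plausibly a loose synonym for serious, and the cited classification, which is not at hand, may well rest on outcome. An article may also leave the detailed criteria for seriousness to the full protocol.

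Much of this stands. The synonym reading is the likelier one, and whether any event would in fact be misfiled cannot be settled from this document. It does not remove the point. Even if the words are synonyms, severity remains the stated basis for seriousness, and it is the wrong basis. Nor is this an omitted detail: the article states a rule and states it badly.

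Three stronger readings are tempting, and the document does not support them.

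- *Serious events will go unrecorded.* Study Design provides for documenting all adverse events at follow-up visits, and the Adverse Event section promises care to anyone who has one.
- *The safety comparison is spoiled.* The criterion in Feasibility Assessment compares the frequency of adverse events of any class, so it does not depend on how they are sorted.
- *The further halting condition is also an error.* Requiring severe toxicity before stopping a trial at once can be a deliberate choice, and infection is a listed risk of the procedure. An automatic halt for every serious event linked to site infection could stop a 30-socket pilot over one expected complication.

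**Conclusion.** The point holds as a fault in the wording of a stated safety rule. Severity is given as the basis for seriousness, and the 24-hour notice and the opening of the halting sentence use severe where the rest of the article uses serious. As written, an event that is serious by outcome and only mild or moderate in intensity need not trigger the notice or be considered under the halting rule.

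The size is modest. No sample size, estimate or error rate changes, and no count of missed events or length of delay is claimed. The conclusion rests on the text as it stands and on the usual distinction between outcome and intensity. It does not assume that the authors intend the unsafe reading; they probably do not. It deserves correction because, in a study with no earlier human data and no separate safety board, the trigger for prompt notice should not depend on guessing what was meant.

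**What to change.** In the section Adverse Event and Severe Adverse Event Assessment:

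1. Delete the words *based on severity* from the classification sentence.
2. Classify seriousness by outcome: death, threat to life, hospital admission or lasting disability.
3. Record intensity as a separate item.
4. Write *serious adverse event* in the heading, in the 24-hour notice and at the opening of the halting sentence, to match Study Design and Feasibility Assessment.

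Leave the rest of the halting condition as it is; how much toxicity or infection should stop the trial is for the sponsor to decide.

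The cost is a wording change, one more field on the adverse-event form and possibly a few more notices to the principal investigator. Sample size, randomisation and the efficacy analysis are unaffected.
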